### **INTRODUCTION**

Bimatoprost 0.03% is a prostamide analogue effective in reducing the intraocular pressure (IOP) and it is able to reduce the IOP of about 33% (31-35%) during the day and of about 28% (29-34%) during the night.

It has been recently introduced in the market a new formulation of bimatoprost at the concentration of 0.01% and no data are currently available about its efficacy and safety over the 24 hours.

The new formulation of Bimatoprost 0.01% contains a lower concentration of active principle and this has been related to a better local tolerability profile, and specifically to a lower incidence of conjunctival hyperemia, with maintained ocular hypotensive efficacy.

The purpose of this study is to investigate the ocular hypotensive efficacy, the tolerability and the effects on blood pressure and heart rate of the new formulation of bimatoprost 0.01% and compare them with those of timolol 0.5%, one of the most widely used first line drugs to treat glaucoma.

## **STUDY DESIGN**

Prospective, randomized, placebo controlled, double masked, cross-over clinical trial

## **STUDY POPULATION**

Ocular hypertensive and open angle glaucoma patients will be recruited for this study. Patients will be either naive to ocular hypotensive medications or in case of ongoing treatments they will undergo adequate washout. Patients naive to ocular hypotensive medications will have to show untreated IOP that, according to the investigators, could be controlled with a topical monotherapy.

## **MATERIALS AND METHODS**

Both ocular hypertensive subjects and glaucoma subjects can be enrolled in this study.

### Inclusion criteria

- Diagnosis of primary open angle glaucoma or ocular hypertension based on the 4th edition of the European Glaucoma Society Guidelines criteria.
- IOP <27 mmHg for untreated newly diagnosed patients
- IOP <22 mmHg for patients on treatment with any hypotensive medication in monotherapy and <27 mmHg after adequate washout.
- Washout IOP have to be >21 mmHg for ocular hypertension subjects while no lower limit of untreated IOP is set for glaucoma patients.

### Exclusion criteria

- Age < 18 years
- Any past or active ocular disease other than glaucoma,
- Closed/barely open anterior chamber angle or history of acute angle closure

- Any cause of secondary elevation of IOP
- Argon or selective laser trabeculoplasty within the last six months
- Any previous ocular surgery, ocular inflammation/infection occurred within three months prior to the pre-trial visit
- Uncontrolled systemic diseases that might require initiating or altering concomitant use of systemic medications that can interfere with the study drugs or with IOP (e.g. beta-adrenergic antagonists, alpha-adrenergic agonists, calcium channel blockers, ACE inhibitors and angiotensin II receptor antagonists)
- Hypersensitivity to benzalkonium chloride or to any other component of the trial drug solutions
- Contraindications to the study drugs including reactive airway disease, chronic obstructive pulmonary disease, sinus bradycardia, second or third degree atrioventricular block, overt cardiac failure, or cardiogenic shock, severe allergic rhinitis and bronchial hyperreactivity.
- Pregnancy, nursing or childbearing potential without using adequate contraception.
- Participation in a clinical trial in the 3 months before the screening visit for the present study.

## **STUDY PLAN AND RANDOMIZATION**

Enrolled patients after having performed the untreated baseline 24-hour curve of IOP and blood pressure will be randomly assigned according to a 1:1 computer-generated randomization code list to one of the 2 treatment groups.

Possible treatments will be either bimatoprost 0.01% at night plus placebo in the morning or timolol 0.5% twice (morning and evening).

After 8 weeks of treatment patients will undergo a on-treatment 24-hour IOP and blood pressure curve and will be then crossed-over to the opposite treatment so that patients treated with bimatoprost 0.01% at night plus placebo in the morning will start treatment with timolol 0.5% twice daily and vice versa. After 8 additional weeks (16 weeks from baseline) a third 24-hour assessment of IOP and blood pressure will be performed.

## **WASHOUT**

Washout time varied according to the ongoing treatment and was 6 weeks for prostaglandin/prostamide analogues, 4 weeks for beta-blockers and alpha-agonists, 2 weeks for carbonic anhydrase inhibitors and miotics.

## **STUDY ENDPOINTS**

Primary endpoint: comparison of the mean 24-hour IOP after 8 weeks of treatment with bimatoprost 0.01% once at night plus placebo once in the morning with that after 8 weeks of treatment with timolol 0.5% twice daily.

Secondary endpoints: the comparison of the mean IOP, BP and HR at each of the 6 timepoints of the 24h curve, the comparison of the mean day (average of the 8:00, 12:00, 16:00 and 20:00 o'clock timepoints) and night (average of the 00:00 and 04:00 o'clock timepoints) IOP, BP and HR, and the comparison of the incidence of adverse events. Additionally the mean 24h systolic and diastolic ocular perfusion pressures (OPP) will be calculated and compared between groups. The ocular perfusion pressure will be calculated as the difference between either the mean 24h systolic or the mean 24h diastolic blood pressure and the mean 24h IOP.

## **SCHEDULE OF THE ACTIVITIES**

At baseline enrolled patients were admitted and performed a 24h IOP, BP and HR curve and were then randomized, according to a 1:1 computer-generated randomization code list, to be treated with either bimatoprost 0.01% administered once at night (08.00pm) + placebo administered once in the morning (at 8.00am) or timolol 0.5% administered twice daily (8.00am and 8.00pm). After 8 weeks of treatment a second 24h IOP, BP, and HR curve was performed and then patients were crossed-over to the opposite treatment (patients on bimatoprost 0.01% + placebo switched to timolol 0.5% twice daily and vice versa) and were followed-up for 8 additional weeks. At the end of the follow-up (16 weeks from baseline and 8 weeks after the cross-over) a third 24h IOP, BP and HR assessment was performed. There was no wash-out between the two treatment phases. The treatment duration in each phase of the study was 8 weeks and long enough to avoid any carry-over effects between drugs. In fact the washout time for topical beta-blockers is known to be 4 weeks and for prostaglandin analogues 6 weeks.

At baseline, week 8 and week 16, patients were admitted and IOP was measured by applanation tonometry at 6 time points over the 24h (in the sitting position by Goldmann applanation tonometry at 8:00, 12:00, 16:00 and 20:00 o'clock, and in the supine position by Perkins

applanation tonometry at 00:00 and 04:00 o'clock). Two additional safety visits were performed at week 4 and 12 and during these visits IOP was measured in the sitting position by Goldmann applanation tonometry at 12.00 o'clock.

The mean of two readings or the median of three readings in case of differences  $>2$  mmHg was reported for the analysis and the same calibrated Goldmann applanation tonometer was used by the same trained investigator in each center throughout the study.

At baseline visit patients' ophthalmic and systemic history was recorded and gonioscopy, pachymetry, and standard automated acromatic perimetry, using the Humphrey 24-2 SITA Standard program, were performed. In addition to the IOP measurements a complete ophthalmological evaluation was performed at baseline and at each follow-up visits including best corrected visual acuity measurement, slit lamp examination, ophthalmoscopy and adverse events recording. At baseline and at week 8 and 16 systolic and diastolic BP and HR have been measured at each of the 6 time points of the 24h curve before the IOP measurements by the same trained investigator. Heart rate was measured manually at the radial artery by counting number of beats in 1 minute and blood pressure was measured manually by sphygmomanometry and it was reported as the mean value of three repeated measurement taken at each timepoint. Additionally patients were asked to give specific answers to the following 3 questions at each follow-up visits: 1) did you notice any redness in your eyes since last visit? 2) did you experience any dry eye or foreign body sensation since last visit? 3) did you experience any eye burning sensation since last visit?

## **STUDY EYE**

If only one eye was eligible as trial eye, that eye was included. If both eyes were eligible only the eye with highest baseline mean 24h IOP was included in the statistical analysis.

## **SUBJECTS EXCLUSION**

Enrolled subjects will be excluded from the study in case of pregnancy, medical reasons at the judgement of the investigator (e.g. changes in concomitant ongoing systemic medications that could interfere with IOP), if the patients decide to terminate the study, in case of no response to the topical hypotensive treatment defined as a  $IOP > 24$  mmHg at any visit after randomization.

## **STUDY MEDICATIONS**

Two masked sets of study medications have been prepared, one set containing bimatoprost 0.01% for the evening administration and placebo for the morning administration and one set containing two bottles of timolol 0.5%, one for the morning and one for the evening administration. Masking, randomization list generation, labelling, blinding, packaging, and shipping of trial medications was handled by Pierrel Research IMP s.r.l..

At baseline, after randomization, 1 masked box containing 3 sets of study medications corresponding to treatment-phase 1 was dispensed to each randomized patient. At the week 8 visit the medications were collected from the patients and a second box containing 3 sets of study medications corresponding of treatment-phase 2 was dispensed to each patient.

During the admissions at baseline and at the week 8 and 16 visits the masked study drugs were administered according to the schedule by the study investigators.

#### **INTRAOCULAR PRESSURE MEASUREMENT**

The IOP will be measured at 8:00, 12:00, 16:00, 20:00, 0:00, 4:00, 8:00 and only at 12.00 during the safety visits 1° and 1B. A maximum deviation of +/-15 minutes from the time schedule is allowed. IOP will be measured by Goldmann applanzton tonometry and will be reported as the average of two readings or as the median of three readings if the first two readings differ more than 2 mmHg. Only 1 calibrated tonometer will be used throughout the study.

#### **COMPLIANCE WITH THE STUDY DRUGS**

A clear explanation to each patient about when and how to use the study medications will be performed by the study investigators before the study beginning. Patients will be asked at each visit about the compliance had with the treatment schedule since the previous visit.

#### **CONCOMITANT MEDICATIONS**

During the study no other concomitant ocular topical medications are allowed. Changes of concomitant medications that, at the judgement of the investigator, can interfere with the IOP (e.g. calcium channels blockers, ACE-inhibitors ecc.). Any concomitant medications have to be recorded in the study CRF.

#### **SAFETY**

Best corrected visual acuity (BCVA) will be checked at each study visit. Any clinically relevant reduction of BCVA will be reported as an adverse event.

Slit lamp biomicroscopy will be performed at each study visit to assess any clinically relevant change in the ocular adnexes or in the eye. Specifically will be evaluated the periorcular skin pigmentation, the eyelashes status, the presence of objective and self reported conjunctival hyperemia, the presence of pigment deposits on the corneal endothelium or the presence of cells and flare in the anterior chamber that will be graded as light=1(3-5 cells) moderate=2 (6-20 cells) and severe= 3 (>20 cells).

Indirect ophthalmoscopy will be performed at baseline and at the last study visit to evaluate the retina and the optic nerve status.

### **STATISTICAL ANALYSIS**

If only one eye was eligible as trial eye, that eye was included. If both eyes were eligible only the eye with highest baseline mean 24h IOP was included in the statistical analysis.

Only patients completing the baseline, 8 weeks and 16 weeks visits (24h IOP assessment visits) were included in the efficacy analysis. All randomized patients taking any amount of the study medication were included in the safety analysis.

Data have been described as mean and 95% confidence interval (CI) for continuous variables and frequencies for categorical variables. IOP data have been analysed by treatment and not by group, thus pooling data obtained from the same treatment irrespectively of the treatment sequence. A multivariate ANOVA model for repeated measures was used to test the null hypothesis that the mean 24h IOP between treatments is not different. The treatment sequence (either first bimatoprost 0.01% + placebo or first timolol 0.5% twice daily) was included in the model as fixed effect to test the interaction between drug and treatment sequence and to explore the presence of potential carry-over effects. Post-hoc between treatments comparisons have been performed by paired t-test or Wilcoxon sign rank test after normality check performed by Shapiro-Wilk test. Categorical variables such as proportions and safety variables have been analyzed using the Pearson Chi-squared test or Fisher exact test as appropriate. Statistical significance was set at the 5% level.

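### The efficacy set keeps only completers, and patients leave the study for high IOP, so entry to the primary comparison depends on the primary outcome; some attenuation of the drug difference is expected

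*Protocol*

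**What the plan says.** - **Primary endpoint (Study Endpoints):** "Primary endpoint: comparison of the mean 24-hour IOP after 8 weeks of treatment with bimatoprost 0.01% once at night" plus morning placebo, against the same measure on timolol 0.5% twice daily.
- **Withdrawal (Subjects Exclusion):** a patient leaves the study "in case of no response to the topical hypotensive treatment defined as a" IOP above 24 "mmHg at any visit after randomization". The section does not say whether one reading or a mean over the curve is meant.
- **Visits (Schedule of the Activities):** the on-treatment 24h curves are at weeks 8 and 16. In addition, "Two additional safety visits were performed at week 4 and 12", each with one IOP reading at 12:00.
- **Efficacy set (Statistical Analysis):** "Only patients completing the baseline, 8 weeks and 16 weeks visits (24h IOP assessment visits) were included in the efficacy analysis".
- **Model (same section):** "A multivariate ANOVA model for repeated measures was used to test the null hypothesis" of equal mean 24h IOP on the two treatments.
- **Safety set (same section):** "All randomized patients taking any amount of the study medication were included in the safety analysis".

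The protocol defines no other efficacy set. It does not say how withdrawn patients' IOP is used.

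**The concern.** Withdrawal is decided on the same variable that the trial compares, and withdrawal before week 16 removes the patient from that comparison. If one drug lowers IOP less, its patients sit closer to the limit and cross it more often. Their high values are then missing from both drugs' means.

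Three things are at stake:
- the estimated difference, which is expected to be pulled towards zero;
- power, because patients are lost and the sample size section states no allowance for that;
- interpretation, because the result describes patients who stayed controlled on both drugs, and non-response does not appear in the efficacy result.

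This is not a detail left to a statistical analysis plan. The protocol fixes the set in explicit words.

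**Working it through.** **1. The plan's own figure.** Inputs from Sample Size Calculation: difference 1.5 mmHg, within-patient SD 2 mmHg, two-sided 5%, power 80%, at least 29 subjects.
- SD of the paired difference = √2 × 2 = 2.83.
- n = (2.83 × (1.96 + 0.84) / 1.5)² ≈ 28 by normal approximation.
- Exact t with n − 2 degrees of freedom: 78.6% power at 29 and 80.1% at 30.

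The stated 29 is reproduced closely enough.

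**2. Who leaves the comparison.**

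| First IOP above 24 mmHg | On-treatment data recorded | In the efficacy set? |
|---|---|---|
| Week 4 | noon reading, first drug | no |
| Week 8 | noon reading and 24h curve, first drug | no; valid curve discarded |
| Week 12 | the same, plus noon reading on second drug | no; valid week 8 curve discarded |
| Week 16 | both curves | not settled; yes if the Statistical Analysis wording is read literally |

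**3. Removal differs by drug.** The protocol gives no on-treatment mean or between-patient SD. Assume a timolol mean of 17 to 20 mmHg, bimatoprost 1.5 mmHg lower, and a between-patient SD of 2 to 3. For a 24h mean, P(above 24) = P(Z > (24 − mean) / √(between² + 2²)).
- Upper end (timolol 20, SD 3): √(9 + 4) = 3.61. Timolol: 4 / 3.61 = 1.11, about 13%. Bimatoprost: 5.5 / 3.61 = 1.52, about 6%.
- Lower end (timolol 17, SD 2): √(4 + 4) = 2.83. Timolol: 7 / 2.83 = 2.47, about 0.7%. Bimatoprost: 8.5 / 2.83 = 3.0, about 0.1%.

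**4. Effect on the difference.** Simulation of 400,000 patients per scenario: patient effect, period-level error SD 2, timepoint SD 1 (assumed), six curve readings and one noon safety reading per period, true difference 1.50 mmHg. The limit was applied either to any single reading, or to the 24h mean and the safety reading only.

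| Patient first above 24 mmHg on the week 16 curve | Completer difference | Attenuation |
|---|---|---|
| Counts as a completer | about 1.31 to 1.48 | 0.02 to 0.19 |
| Does not count | 1.24 to 1.48 | 0.02 to 0.26 |

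In the worst cells (timolol mean 20, any single reading) 77% to 83% complete on the first reading of the rule and 72% to 78% on the second.

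**5. Power.**
- Loss of patients alone: 10% loss leaves 29 × 0.9 ≈ 26, power 73.7%. A 20% loss leaves 29 × 0.8 ≈ 23, power 67.9%.
- To keep 29 completers: 29 / 0.9 = 32.2, so 33 randomised; 29 / 0.8 = 36.3, so 37.
- Loss and attenuation together, week 16 exceedances not counted as completers: about 54% to 78% with 29 randomised, for 1% to 30% removed. Assumptions: bimatoprost mean 16 to 18, between-patient SD 2 to 3, single-reading SD 1.5.

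**6. Limits of the effect.**
- True difference 0: the completer difference stays at 0 and type I error at about 5%.
- Strongly unequal SDs (2.5 to 3 on the better drug, 1 to 1.5 on the worse): the completer difference rises to 1.55 to 1.74. The sample size section assumes one SD.

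**7. Which remedy works.** Same assumptions as step 4.
- Mixed model on patients with at least one 24h curve: 1.31 to 1.48, essentially the completer result. Withdrawals at weeks 4 and 12 depend on noon readings that this model never sees.
- Mixed model that also takes the reading at the visit triggering withdrawal: about 1.50 to 1.53. This assumes that the noon reading shares the level of its period.

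**The case against.** The strongest reply is that material bias is possible but not shown. The protocol gives neither a removal rate nor an on-treatment mean. The entry criteria cap IOP below 27 mmHg untreated or after washout, and below 22 mmHg on existing monotherapy. Naive patients must be judged controllable on one drug. At a timolol mean of 17 mmHg, with a week 16 exceedance counted as completion, the loss is only about 0.02 to 0.06 mmHg. A within-patient comparison also needs both periods, and model details are often left to an analysis plan.

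The point about size stands, and the upper end of the ranges should not be read as a forecast. The rest does not remove the defect, because the completer restriction and the IOP-based withdrawal are both stated.

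Three stronger readings are tempting, and the documents do not support them:
- **That the rule certainly shrinks the difference.** It does so under the planning model. It has no such effect if the drugs are equal, and the direction could reverse if the SDs differ strongly.
- **That it risks a false positive.** The planned test is "to test the null hypothesis that the mean 24h IOP between treatments is not different", and under that null, with a common SD, removal is balanced between the drugs.
- **That every patient ever above 24 mmHg is dropped.** A patient who first exceeds the limit on the week 16 curve has completed all three curves. The two sections leave that patient's status open.

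**Conclusion.** The point holds. Selection into the primary comparison depends on the primary outcome variable, and valid on-treatment curves are discarded. Given a true difference of 1.5 mmHg and one within-patient SD of 2 mmHg, the expected completer difference is about 1.31 to 1.48 mmHg, or 1.24 to 1.48 if week 16 exceedances also count as removals. That is a loss of 0.02 to 0.26 mmHg (1% to 17% of 1.5), together with lower power and non-response that the efficacy result does not show. The existence of the selection follows from the text. Its size rests on the assumed timolol mean (17 to 20 mmHg), between-patient SD (2 to 3) and timepoint SD (1).

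**What to change.** Leave the clinical withdrawal rule unchanged and separate it from the analysis set.

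1. Define the primary efficacy set as all randomised, treated patients with any on-treatment IOP. Requiring a 24h curve is not enough, because it still loses every week 4 failure.
2. Replace the multivariate ANOVA with a linear mixed model: fixed treatment, period and sequence, random patient. Use every recorded on-treatment curve and the IOP at the visit that triggers withdrawal. Where no 24h curve exists for that treatment, use the single 12:00 reading from week 4 or 12.
3. Report withdrawals for IOP above 24 mmHg by treatment.
4. Keep the completer analysis as a sensitivity analysis.
5. Reconcile Subjects Exclusion with Statistical Analysis on whether a patient first above 24 mmHg at week 16 is a completer.

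**Cost:** wording in those two sections and a standard model; no extra patients or visits. For week 4 and week 12 failures, one noon reading stands in for a 24h mean. If noon IOP differs systematically from the 24h mean, that substitution adds its own error. The model also assumes data missing at random given the observed IOP. That assumption cannot be verified, but it is weaker than the one behind the completer analysis.

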### **SAMPLE SIZE CALCULATION**

It has been estimated that the probability is 80% that a sample size of at least 29 subjects in this cross-over study will allow to detect a between treatments difference at a two-sided 5% significance level if the true difference is 1.5 mmHg or greater. This is based on the assumption that the within-patient standard deviation of the response variable is 2 mmHg.

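### The paired tests for the continuous secondary comparisons leave out period, which biases them if the analysed sequences are unequal and costs power if they are equal

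*Protocol*

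**What the plan says.** STUDY DESIGN describes a "Prospective, randomized, placebo controlled, double masked, cross-over clinical trial". Patients are "randomly assigned according to a 1:1 computer-generated randomization code list to one of the 2 treatment groups" and change to the other treatment after 8 weeks, so this is a two-period, two-sequence design.

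STATISTICAL ANALYSIS sets three things that bear on this point:

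- The pooling rule: "IOP data have been analysed by treatment and not by group, thus pooling data obtained from the same treatment irrespectively of the treatment sequence".
- The follow-up tests: "Post-hoc between treatments comparisons have been performed by paired t-test or Wilcoxon sign rank test after normality check performed by Shapiro-Wilk test".
- The efficacy set, which is limited to patients who completed all three 24-hour assessments.

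Sequence, and its interaction with drug, enters only the repeated-measures ANOVA of mean 24-hour IOP. The protocol presents that term as a check on interaction and carry-over. No period term is named anywhere in the section.

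The secondary endpoints include "the comparison of the mean IOP, BP and HR at each of the 6 timepoints of the 24h curve", and the day and night means of the same variables. The paired tests are the only between-treatment method the protocol names for these continuous comparisons.

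**The concern.** In a 2x2 cross-over each patient's treatment difference also contains the difference between the two periods, with opposite sign in the two sequences. A one-sample paired test averages these differences without regard to sequence. The period effect cancels from the mean only if the two sequences contribute equal numbers. Even then it stays in the spread of the differences, and so in the estimated standard error.

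Allocation is 1:1, but nothing keeps the analysed sequences equal. Patients can leave after randomization under SUBJECTS EXCLUSION, and only completers are analysed. At stake are the timepoint, day and night results, which describe the 24-hour profile the study was set up to examine. A shift between the second and third 24-hour admissions could move these estimates, or widen their intervals, for reasons unrelated to drug.

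**Working it through.** **Inputs.** From SAMPLE SIZE CALCULATION: "the probability is 80% that a sample size of at least 29 subjects in this cross-over study"; the aim to "detect a between treatments difference at a two-sided 5% significance level if the true difference is 1.5 mmHg or greater"; and the assumption that "the within-patient standard deviation of the response variable is 2 mmHg". The variance of a within-patient difference is then 2 × 2² = 8 (SD 2.83 mmHg). The protocol gives no period effect, so 0.5, 1 and 2 mmHg are assumed. The SD and target difference are those of the primary sample-size calculation, borrowed here for timepoint IOP.

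**The plan's own figure.** n = 2 × 2² × (1.960 + 0.842)² / 1.5² = 27.9, so 28 by the normal formula. With the t distribution, power at n = 29 is 78.7%. The stated 29 reproduces.

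**Expectation.** Let δ be bimatoprost minus timolol and π be period 2 minus period 1. The expected within-patient difference is δ − π in the bimatoprost-first sequence (BT) and δ + π in the timolol-first sequence (TB). Therefore:

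- Pooled paired mean: δ + π(n_TB − n_BT)/n.
- Expected sample variance of the differences: 8 + 4π²·n_BT·n_TB / [n(n − 1)].
- Mean of the two sequence means: δ, with no π in it.
- Half the difference between the sequence means (TB minus BT): π. This is the drug-by-sequence contrast, so in this design that term is the period contrast.

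**Bias in mmHg**, shown as BT/TB. At 15/14 it is π/29 in size: 0.5/29 = 0.02, 1/29 = 0.03, 2/29 = 0.07. At 17/12 it is 5π/29: 0.09, 0.17, 0.34. At 15/15 it is zero.

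**Variance at 15/15.** 4 × 15 × 15/(30 × 29) = 1.034, so the expected variance is 8 + 1.034π²: 8.26, 9.03 and 12.14. With fixed, equal sequences the true variance of the paired mean is still 8/30. Only its estimate is too large, which makes the test conservative.

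**Power at δ = 1.5 mmHg.** Simulation with 100,000 or more trials per scenario. The paired t-test has n − 1 df; the period-adjusted contrast (mean of the two sequence means, pooled within-sequence variance) has n − 2 df.

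| Split and direction | π = 0.5 | π = 1 | π = 2 | Period-adjusted |
|---|---|---|---|---|
| 15/15 | 79% | 77% | 65% | 80% |
| 15/14, bias opposes drug | 77% | 73% | 58% | 79% |
| 17/12, bias opposes drug | 73% | 64% | 39% | 77% |
| 12/17, bias favours drug | 82% | 84% | 84% | 77% |

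**Type I error of the paired t-test.** At 15/15 it is about 3.8% at π = 1 and 1.7% at π = 2. At 17/12 it stays below 5% at every value tried. It clearly exceeds 5% only at 19/10: 7.2% at π = 1 and 11% at π = 2. The period-adjusted contrast stays at about 5% throughout.

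**Cost of adjusting when π = 0.** At n = 30, 80.2% against 80.1%. At 17/12, 78.5% against 77.3%. At 19/10, 78.9% against 74.5%.

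**The case against.** The strongest reply is that the primary test is not exposed in this way and that the rest is modest.

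- **Primary analysis.** A reader might infer that the primary result is compromised. The document does not support that. The ANOVA of mean 24-hour IOP carries sequence and drug-by-sequence, which can absorb a period effect. This stands, provided the term is kept in the model from which the treatment effect is read.
- **False positives.** A reader might infer that period inflates type I error even with equal sequences. The reverse is true: the test is then conservative. The 11% figure needs both a 19/10 split and a 2 mmHg effect, and the protocol has no dropout figure that points to such a split.
- **Size.** The assumed 2 mmHg is larger than the 1.5 mmHg drug difference sought. At 0.5 mmHg with equal sequences the loss is about one power point. Unequal sequences can also raise apparent power, although the gain comes from bias.
- **Likelihood.** Every patient has a 24-hour admission at baseline before period 1, and measurement is standardised. Both make a period effect less likely. Neither excludes one.
- **Scope.** The pooling sentence names only IOP; for BP and HR the point rests on the sentence about post-hoc tests. Categorical and safety variables are tested by chi-squared or Fisher, so the point does not cover every comparison.
- **Normality check.** Choosing the test after Shapiro-Wilk may also invite criticism, but no harm from it has been quantified and this point does not rest on it.

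These replies narrow the point. They do not give the paired tests a period term.

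**Conclusion.** The point holds for the continuous post-hoc and secondary comparisons. The tests the protocol fixes for them ignore period. They are biased by π(n_TB − n_BT)/n if the analysed sequences differ in size, and lose power if they do not.

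The algebra is certain; the practical impact is not. Near balance the bias is small (at most 0.07 mmHg at 15/14 over the assumed range) and the main cost is power. At 17/12 the bias reaches 0.17 mmHg for a 1 mmHg period effect and 0.34 mmHg for 2 mmHg. All these sizes rest on assumed period effects and on the SD and difference of the primary sample-size calculation. The documents give no SD, target difference or period effect for BP or HR, so the effect there cannot be quantified. This is a worthwhile, low-cost improvement and does not undermine the primary conclusion.

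**What to change.** In STATISTICAL ANALYSIS, replace the paired tests for continuous follow-up comparisons with a period-adjusted cross-over contrast. Two forms serve:

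- a mixed model with treatment, period and sequence; or
- a two-sample t-test between sequences on within-patient period differences (period 1 minus period 2). The expected values are δ − π in BT and −δ − π in TB, so half their difference is δ and π cancels.

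For the nonparametric version, use the Wilcoxon rank-sum test on the period differences by sequence in place of the signed-rank test. State also that the drug-by-sequence term stays in the primary ANOVA.

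No new data are needed, because sequence is already in the primary model. Near balance the cost is one degree of freedom. At a 19/10 split it is about 4 power points if there is no period effect.

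### The drug-by-sequence interaction, the one term named for testing beside the carry-over aim, is the period effect; the contrast that does measure differential carry-over is in the model but not named

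*Protocol*

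**What the plan says.** The Study Plan and Randomization section describes two sequences of two 8-week phases, with patients "randomly assigned according to a 1:1 computer-generated randomization code list to one of the 2 treatment groups" and then crossed to the other treatment. The Schedule of the Activities section states: "There was no wash-out between the two treatment phases". It goes on to argue that "The treatment duration in each phase of the study was 8 weeks and long enough to avoid any carry-over effects between drugs", citing washout times of 4 weeks for topical beta-blockers and 6 weeks for prostaglandin analogues.

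The Statistical Analysis section gives the primary test: "A multivariate ANOVA model for repeated measures was used to test the null hypothesis that the mean 24h IOP between treatments is not different". Treatment sequence enters as a fixed effect "to test the interaction between drug and treatment sequence and to explore the presence of potential carry-over effects". On pooling it says: "IOP data have been analysed by treatment and not by group, thus pooling data obtained from the same treatment irrespectively of the treatment sequence". Post-hoc comparisons are paired t-tests or Wilcoxon tests. The protocol names no period effect, and it does not say which model term is to be read as carry-over.

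**The concern.** The sentence puts the drug-by-sequence interaction next to carry-over and names nothing else to be tested, so an analyst would most naturally read that interaction as the carry-over check. In this design it does not do that job.

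Two misreadings could follow. An ordinary shift in IOP between weeks 8 and 16 could be reported as carry-over. A non-significant interaction could be taken as reassurance about a bias to which the term gives no weight. With no washout between phases, this sentence holds the only statistical look at carry-over in the protocol, so the label on the term affects how the result is interpreted.

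**Working it through.** **Inputs from the protocol.** Two sequences, allocated 1:1 (Study Plan and Randomization). At least 29 patients, within-patient SD 2 mmHg, difference 1.5 mmHg, two-sided 5%, 80% power (Sample Size Calculation).

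**Assumptions.** A 15/14 split of the 29; period shifts and carry-overs of 1.0 to 1.5 mmHg; between-patient SD of 1.5, 2 or 3 mmHg. The protocol gives none of these.

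**The plan's own figure.** n = 2 × 2² × (1.960 + 0.842)² / 1.5² = 27.9, so 28 patients by the normal approximation. By noncentral t, 29 patients give 78.6% to 78.7% power and 30 give just over 80%. The stated 29 is reproduced to within one patient, and nothing below changes it.

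**Cell means.** Let tB and tT be the drug effects, π the shift from period 1 to period 2, and lB and lT the carry-over of bimatoprost and timolol into period 2.

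| Sequence | Period 1 | Period 2 |
|---|---|---|
| Bimatoprost first | μ + tB | μ + tT + π + lB |
| Timolol first | μ + tT | μ + tB + π + lT |

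**Contrasts.** The bimatoprost-minus-timolol difference is tB − tT − π − lB in the first sequence and tB − tT + π + lT in the second.

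- Drug-by-sequence (first minus second): −2π − (lB + lT). The weight on lB − lT is zero.
- Sequence main effect (difference between the within-patient sums): lB − lT.
- Treatment (average of the two differences): tB − tT + (lT − lB)/2.

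The bias in the treatment contrast is therefore (lT − lB)/2, and only the sequence main effect measures it.

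**Rejection rate of the interaction test.** SE = √8 × √(1/15 + 1/14) = 2.828 × 0.3716 = 1.051, with 27 df.

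| Scenario | Contrast | Contrast/SE | Significant at 5% |
|---|---|---|---|
| Period shift 1.0, no carry-over | 2.0 | 1.90 | 45% |
| Period shift 1.5, no carry-over | 3.0 | 2.85 | 79% |
| lB = +0.75, lT = −0.75, no period shift | 0 | 0 | 5% |
| Carry-over 1.5 from one drug only, no period shift | 1.5 | 1.43 | 28% |

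(Contrasts are in absolute value.) In the third row the treatment estimate is biased by 0.75 mmHg, half the 1.5 mmHg design difference. Simulation with 20,000 runs per scenario agrees: 78% to 79% for the second row, about 5% for the third and about 28% for the fourth.

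**Power of the sequence contrast.** SE = √(4·SDb² + 8) × 0.3716, where SDb is the between-patient SD.

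| SDb (assumed) | SE | Power for lB − lT = 1.0 | Power for lB − lT = 1.5 |
|---|---|---|---|
| 1.5 | 1.53 | 9.7% | 16% |
| 2 | 1.82 | 8.3% | 12% |
| 3 | 2.46 | 6.8% | 9% |

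**Effect on the treatment estimate.** With sequences weighted equally, π cancels from the treatment contrast, as shown above. In a raw pooled comparison with 15 patients on bimatoprost first and 14 on timolol first, the residual is (−15π + 14π)/29 = −π/29, or 0.05 mmHg in size for a 1.5 mmHg shift.

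**The case against.** A reader might infer that the trial's only carry-over check tests the wrong thing. The text does not support that. The sentence joins two aims with an *and*, and sequence is itself a fixed effect, so its main effect, the standard carry-over contrast, is already in the model. The sentence can be read as two separate examinations, which makes it ambiguous rather than plainly wrong. What remains is that the interaction is the only term named for testing, and the sequence main effect is never identified as the carry-over contrast.

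A reader might also infer that the missing period term corrupts the primary analysis. It does not. Treatment, sequence and their interaction saturate the same four cell means as treatment, period and sequence. The model's treatment contrast is therefore already period-adjusted when sequences are weighted equally.

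Nor is the interaction blind to all carry-over. It responds to carry-over from one drug alone (about 28% rejection at 1.5 mmHg), although it cannot separate this from a period shift. The 5% figure needs carry-overs of equal size and opposite sign, a limiting case that the protocol gives no reason to expect.

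Three further points stand. The protocol says it will explore carry-over and attaches no decision rule to the result. The 8-week phases exceed both cited washout times, and the 24-hour curves are taken at the end of each phase. The correct contrast has little power, so naming it adds clarity rather than protection.

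It could also be said that such detail belongs in a statistical analysis plan. But the protocol itself names the term and places it beside carry-over, so the point concerns what is stated, not what is left out.

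**Conclusion.** The concern holds as a mislabelled or ambiguous check, of moderate severity. The algebra is exact for this design: drug-by-sequence equals −2π − (lB + lT), and the differential carry-over that biases treatment by (lT − lB)/2 is found only in the sequence main effect. On the most natural reading of the sentence, a pure period shift of 1.0 to 1.5 mmHg would be called carry-over in about 45% to 79% of trials, and equal and opposite carry-overs would be flagged no more often than chance.

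Those rates rest on the protocol's n of 29 and SD of 2 mmHg, plus assumed shifts and a 15/14 split; the power of the sequence contrast also rests on an assumed between-patient SD. The consequence is for interpretation: the model's treatment estimate and the sample size are essentially unaffected. The case against carry-over rests mainly on phase length, and no test in this trial could replace it.

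**What to change.** Reword the Statistical Analysis section as follows.

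- State the model as fixed treatment, period and sequence, with patient within sequence as a random effect.
- Say that the drug-by-sequence interaction is the period effect (aliased with the sum of the carry-overs), and report it as such.
- Report the sequence contrast lB − lT with its 95% CI, tested against between-patient error, as the carry-over estimate.
- State that this test has low power (about 7% to 10% for 1 mmHg if the between-patient SD is 1.5 to 3 mmHg, an assumption), that it does not decide how treatment is analysed, and that the argument against carry-over rests on the 8-week phase length.
- Take the treatment effect and its 95% CI from the period-adjusted within-patient contrast.

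The cost is wording only. The data, the fitted cell means, the degrees of freedom and the number of patients stay the same.
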